## Abstract

**Background:**

Falls are common adverse events in residential care facilities. Commonly reported figures indicate that at least 50% of residents fall in a 12 month period, and that this figure is substantially higher for residents with dementia. This paper reports the protocol of a project which aims to implement evidence based falls prevention strategies in nine residential aged care facilities (RACFs) in Australia. The facilities in the study include high and low care, small and large facilities, metropolitan and regional, facilities with a specific cultural focus, and target groups recognised as being more challenging to successful implementation of falls prevention practice (e.g. residents with dementia).

**Methods:**

The project will be conducted from November 2007-November 2009. The project will involve baseline scoping of existing falls rates and falls prevention activities in each facility, an action research process, interactive falls prevention training, individual falls risk assessments, provision of equipment and modifications, organisation based steering committees, and an economic evaluation. In each RACF, staff will be invited to join an action research group that will lead the process of developing and implementing interventions designed to facilitate an evidence based approach to falls management in their facility. In all RACFs a pre/post design will be adopted with a range of standardised measures utilised to determine the impact of the interventions.

**Discussion:**

The care gap in residential aged care that will be addressed through this project relates to the challenges in implementing best practice falls prevention actions despite the availability of best practice guidelines. There are numerous factors that may limit the uptake of best practice falls prevention guidelines in residential aged care facilities. A multi-factorial individualised (to the specific requirements of each facility) approach will be used to develop and implement an action plan in each participating facility based on the best available evidence.

## Background

Falls are common adverse events in residential aged care facilities (RACFs). Reported figures indicate that at least 50% of residents fall in a 12 month period, and that this figure is substantially higher in some at risk populations such as people with dementia where the incidence is 70-80% [1]. Injuries from falls are also more common for RACF residents than for older people living in their own home, with a study by Kallin et al (2002) reporting injuries associated with 54% of falls, and a third of injuries being fractures [2]. Another study identified that over half of the fractures sustained from falls by residents were hip fractures, which have an enormous associated personal and societal cost [3]. Although accurate cost data is not available for costs associated with falls in RACFs in Australia, some data from Europe estimates the costs associated with falls in residential care to be 994EURO/fall (approximately $AUD1,560) [4].

There are clear benefits of a multiple strategy approach to falls reduction for older people in residential care settings, both as an intervention and prevention strategy [5]. Randomised trials have shown that multifactorial interventions, either based on falls risk assessments, or a range of general interventions introduced for all residents can reduce falls in residential care settings [6-8]. Single interventions including medication review [9], vitamin D supplementation [10,11], continence management combined with functional training [12], and staff education [13] have also been shown to reduce falls. Other interventions such as exercise have had mixed outcomes in residential care settings [14-16]. Approaches such as providing information for residents and carers, and strategies to improve observation or surveillance of at risk residents (e.g. bed and chair alarms) are recommended as part of best practice in residential care settings, although there are no randomised trials evaluating the effectiveness of these approaches [5].

Previous reviews have shown that the involvement of staff, the method of training provision, staff awareness of falls and staff implementation of evidence based strategies to prevent falls and falls related injuries are areas requiring further exploration [5,17].

Despite the availability of evidence-based guidelines for implementing falls prevention and other interventions in residential aged care, there is moderate evidence that these interventions are not routinely or easily incorporated into routine practice. For example, in a study aiming to implement pain management guidelines and falls prevention guidelines in residential care settings, less than 45% of facilities participating in a training program regarding the guidelines actually implemented the one or the other of the guidelines [18]. While there was some evidence of practice change in line with the guidelines in some of the facilities, a range of barriers to implementation were identified.

Action research is an approach that could be useful in engaging staff in falls prevention interventions and for achieving sustainable practice change. Action research is a process where staff are supported to undertake an investigation into their current practice, recognise problems, envisage possible solutions and take action with the intentions of working towards addressing the problem. Utilising this approach, groups of staff collaborate to take action to identify context specific issues, identify and implement an evidence based approach and in the process support and challenge each other to make progress on the problem [19]. Action research is a method of choice when a group of people have a desire to work collaboratively to develop new understandings of their situation to address practical problems through locally specific and contextually appropriate forms of action [20-22].

In addition to limitations implementing evidence based practice, few studies have investigated the financial implications of falls prevention strategies in the residential care setting [5].

The primary aim of the project is to implement evidence based falls prevention guidelines in nine RACFs in Australia with the intent to reduce falls and falls-related injuries. The approach to be adopted involves multiple strategies to improve falls management. These include: improving RACF staff knowledge and attitudes with respect to falls risk; actively engaging a core group of staff in a process of designing, implementing and evaluating local specific interventions to reduce falls in the context of their participation in action research falls groups in each RACF, and; identifying a range of falls risk factors for individual residents (e.g. undertaking falls risk assessments) and for facilities (e.g. environmental falls risk factors). This project also encompasses an economic evaluation for which additional data to support economic variables will be collected.

The project is funded by the Australian Government Department of Health and Ageing, as part of the "*Encouraging Best Practice in Residential Aged Care*" (EBPRAC) program. The EBPRAC program aims to improve evidence-based clinical care for residents in aged care homes and to enable nationally consistent application of this care.

## Method

The project will involve baseline scoping of existing falls rates and falls prevention activities in each RACF, an action research process, interactive falls prevention training, individual falls risk assessments, provision of equipment and modifications, organisation based steering committees, and an economic evaluation. In all RACFs a pre/post design will be adopted with a range of standardised measures utilised to determine the impact of the interventions. The study involves fostering ownership by each facility of an evidence based, best practice falls prevention approach through involvement of staff in partnership with experts in falls prevention using best practice resources to guide the process.

### Recruitment of facilities and participants

RACFs were approached in three states across Australia, and all accepted the invitation to participate in the project. These facilities were selected purposively to represent a range of sizes, target groups, and geographic features, including high and low level care, dementia specific, rural/regional, metropolitan, ethnic specific or psychogeriatric. All except one facility are not for profit organisations and some are linked to health services. Across the nine participating facilities approximately 670 people reside and 650 staff are employed. All staff and residents will be invited to take part in at least one component of the project.

Each facility is allocated funding to release a nurse staff member to the role of key contact and project support person known as the falls resource nurse (FRN, 0.1 EFT) for the project. The secondment provides an opportunity for the staff member to undertake project activities without being distracted from their existing workload. It is anticipated that this process would contribute to ongoing sustainability through building capacity within the facility. An additional 0.1 EFT funding is provided to support other areas of staff time and engagement in specific falls prevention activities.

With the assistance and advice of the FRN in each of the facilities, residents and families will be informed of the research. Methods of informing and engaging residents and families will include attendance at family meetings, flyers distributed on family and resident notice boards and distribution of project information through facility mail outs.

### Procedure

#### Baseline scoping

To gauge how well facilities are currently implementing evidence based practice, a comprehensive scoping audit will be undertaken at the beginning of the study. This will include: falls incident data, an audit of the current falls prevention activities, environmental audits, a survey on resident safety culture within the organisation and a questionnaire on sustainability.

From each facility, falls data for the six months preceding project commencement will be analysed, including data on circumstances, precipitating factors, consequences and management. These will be reported as falls/1000 resident bed days. Frequency analyses will be used to determine the most common locations, circumstances and consequences of falls.

The falls scoping audit was developed using key falls prevention strategies identified in the Victorian Quality Council's falls prevention guidelines [23] and covers issues such as falls risk assessment, collection and use of falls prevention data, and access to allied health staff. Key interventions covered in the audit include: group exercise, individual exercise, walking aids, hip protectors, medication review, vitamin D and calcium supplementation, toileting assistance program, adequate condition and use of aids for sensory loss, feet in good condition and appropriate footwear, surveillance, hi-lo or lo-lo beds and referral to other health professionals. The Project Officer will send the survey to the FRN to complete. After the FRN completes the survey, the Project Officer will go through it with the FRN to make sure everything is completed and that the Project Officer has full knowledge of the falls prevention activities taking place in the facility.

To identify environmental hazards that may require modification, environmental audits will be completed in each facility. This will involve an audit of resident rooms, indoor and outdoor communal areas of each facility using an environmental audit tool adapted from a tool developed to improve the environment for older people in health services [24]. Recommendations from the environmental audits will be made to participating facilities, and used to assist in the allocation of funds available for environmental modifications as part of the project.

A safety culture survey for residential aged care facilities will be used to assess safety culture and hazard reporting at baseline to inform action research. This survey has been adapted from the safety culture survey for hospitals [25]. The survey will be researcher administered to all facility staff working within a 24 hour period, including staff working on night, day and evening shifts.

To measure how each facility will sustain project activities, the sustainability model questionnaire will be completed with the action research groups [26].

At the completion of the scoping phase, an individualised report will be provided to each facility, highlighting areas being well implemented, and areas where additional activity needs to be targeted. This will form the basis for the Action Research Groups to identify gaps in evidence based practice to address in the implementation phase within each facility.

#### Action research

An action research approach will be used in the facilities as a key element to work towards achieving the project aims. In each RACF staff interested in falls prevention will be invited to join a falls action research group (FARG). To recruit staff, meetings will be held in each RACF to identify volunteers. Eligibility for FARG membership will include any staff member working within the facility (for example, nurse, personal carer, lifestyle, allied health, kitchen, laundry, cleaning staff, management). In some instances it might be relevant to include staff who may not work in the facility but visit on a clinical basis such as a physiotherapist. Five-six staff members will be recruited in each FARG. A project officer will facilitate meetings that will be audio taped and transcribed. The project officer will conduct a first level analysis that will be distributed to the respective FARG members prior to the next meeting to ensure the discussion has been recorded accurately and key points included.

From May 2008 FARG members will meet fortnightly for 12 months to identify key issues, facilitators and barriers to successful falls prevention within their RACF. During these discussions the members will articulate their position on the issues that impact on the occurrence of falls in their facility. Each FARG will draw on findings together with the audit data to determine site specific activities on which to focus their interventions to improve falls prevention in the RACFs.

These activities will be developed into action plans that the FARGs will then implement with support and advice from the project officer. Methods for evaluating these actions will be established and monitored by the FARGs. Project officers will assist in writing up action plans incorporating evaluation measures.

The project officers facilitating the FARGs in each RACF will also maintain a qualitative record of the group's activities or project diary that will provide useful data for determining factors that enabled or prevented the success of the falls interventions. This will be supplemented with thematic analysis of transcripts using NVivo software.

To measure FARG participants' perception of professional clinical practice (such as communication, leadership, teamwork, control) the Revised Professional Practice Environment Scale (RPPE) [27] will be used. It will be distributed and collected by project officers at the first and last FARG meetings for all action research staff to complete.

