#### Evaluation

Falls incident data will be reviewed by the project team on a six monthly basis throughout the project and will be reported back to facilities at six and 18 months. As previously described, each FARG will also develop and complete site-specific evaluations relevant to the action plan implemented. After completion of the FARGs, the sustainability model questionnaire, the falls scoping survey and the safety culture survey will also be readministered to gauge any other changes during the project.

Final resources for dissemination of project processes and outcomes will be developed and disseminated. Findings will be collated into facility specific reports for facilities to review outcomes as well as an overall final evaluation report combining data from all sites and incorporating the economic evaluation.

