## Discussion

Despite the availability of evidence-based guidelines for implementing falls prevention interventions in residential aged care, there is moderate evidence that these interventions are not routinely incorporated into routine practice. This project aims to provide a comprehensive multifaceted strategy to try to increase uptake of evidence based guidelines in the participating facilities. In line with the research evidence, a multi-factorial, individualised (to the specific requirements of each facility) and all of facility approach is planned to develop and implement an action plan based on the best available evidence in the participating facilities. We will explore the effectiveness of this approach in a range of facilities including dementia specific and psychogeriatric, in which there is limited research of effective approaches to falls prevention.

An action research approach will be used to assist in engaging staff in practice change, encouraging them to identify better practice strategies, implement and evaluate the outcomes in their own practice. It is anticipated that this approach will be useful for empowering staff and facilitating sustainable evidence based falls prevention interventions.

The collection of falls data, and an economic evaluation determining the costs of the implementation and modelling of potential cost savings through the impact of project activity will also inform whether there are economic benefits of investing in these activities. With these data, other RACFs would find it more compelling to follow a similar approach to falls minimisation.

There are numerous factors that may limit the uptake of best practice falls prevention guidelines in RACFs, including lack of knowledge among staff, residents and families that many falls are preventable and the type of interventions that can be effective; lack of optimisation of staff routines and practice; unsupportive/unsafe environments; lack of adequate falls incident reporting and analysis at the local level; and lack of staff time. This multi-factorial approach, inclusive of staff as key drivers within each facility, will implement an evidence based falls prevention project across nine Australian RACFs that aim to reduce falls and falls-related injuries.

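### Both RPPE measurements are tied to attendance at the first and last FARG meetings, with no described route to a follow-up score for members who leave or are absent

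*Protocol article*

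**What the plan says.** All of this is in the Protocol article.

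- **Collection rule (Action research).** The RPPE measures how members of the falls action research group (FARG) see their practice environment, for example leadership and teamwork. On timing and route the text says: "It will be distributed and collected by project officers at the first and last FARG meetings for all action research staff to complete".
- **Interval (Action research).** "From May 2008 FARG members will meet fortnightly for 12 months".
- **Group size and recruitment (Action research).** "Five-six staff members will be recruited in each FARG", and "To recruit staff, meetings will be held in each RACF to identify volunteers". There is one group in each of the nine facilities.
- **After the groups end (Evaluation).** The instruments to be repeated are listed: "the sustainability model questionnaire, the falls scoping survey and the safety culture survey will also be readministered". The RPPE is not in this list.
- **Analysis (Analysis).** Questionnaires and surveys are to be analysed with suitable non-parametric methods. Whether the RPPE comparison is paired is not stated.
- **Another instrument (Training and support).** The knowledge test for falls resource nurses is returned by e-mail one week after training, so the project already uses a return route outside meetings.

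**The concern.** The sentence on the RPPE names its target as all action research staff, but the procedure reaches that target only if every member attends two particular meetings about a year apart. Someone who withdraws, changes job or is off shift on the closing day has no described way to give a second score. Someone who joins after the first meeting has no first score.

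The RPPE asks about matters such as teamwork, leadership and control, which could plausibly influence whether a volunteer stays in the group. Missing closing scores may then be related to the change being measured. The design is pre/post with no comparison group described, so selective follow-up could not be separated from real change. What is at stake is how the RPPE change is read: as the average change among the staff recruited, or as the change among those who were there at the end.

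**Working it through.** The document gives no sample size, power or attrition figure for the RPPE, so there is no figure of the plan's to reproduce. The check has two parts: what the text allows, and an illustration of size.

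**1. What each analysis would estimate if the text is followed as written**

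- *Paired.* A change score needs a form from both meetings, so the result describes members present at both.
- *Unpaired.* The first set includes later leavers, and the second may include late joiners. The difference combines change within people with a change in who is being asked.
- Neither is the average change among all recruited members, unless nobody is lost or loss is unrelated to perception.

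**2. Inputs from the document**

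- Groups: 9 (Background: "implement evidence based falls prevention guidelines in nine RACFs in Australia"). Members per group: 5-6.
- Members in all: 9 × 5 = 45 to 9 × 6 = 54.
- Fortnightly meetings over 12 months: 52 / 2 = 26, approximately.
- One member per group without a closing form: 1/6 to 1/5, that is 17-20%.

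**3. Assumptions (not in the document)**

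- Proportion p without a closing score: 17% to 40%.
- Gap d, stayers' mean change minus leavers' mean change: 0.3 to 0.5 SD of the change score. The sign is also assumed.
- True mean change among all N recruited members: zero.
- A one-sample t-test stands in for the unspecified non-parametric test. Clustering by facility is ignored.

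**4. Formulas**

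- The overall mean change is (1 − p) × stayers + p × leavers, so bias of the stayers' mean = p × d.
- Members with both scores: n = N(1 − p), rounded. Standard error in SD units = 1/√n, so bias/SE = p × d × √n.
- Rejection probability at two-sided 5%: non-central t on n − 1 df with non-centrality p × d × √n.

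**5. Results**

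| N | p | d | n | Bias (SD) | Bias/SE | Rejection | Share of rejections that are false gains |
|---|---|---|---|---|---|---|---|
| 45 | 1/6 | 0.3 | 38 | 0.05 | 0.31 | 6.0% | 80% |
| 54 | 1/6 | 0.5 | 45 | 0.083 | 0.56 | 8.5% | 93% |
| 54 | 0.20 | 0.5 | 43 | 0.10 | 0.66 | 9.8% | 95% |
| 45 | 0.40 | 0.3 | 27 | 0.12 | 0.62 | 9.2% | 94% |
| 54 | 0.40 | 0.5 | 32 | 0.20 | 1.13 | 19.5% | 99% |

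Over all twelve combinations of N (45, 54), p (1/6, 0.20, 0.40) and d (0.3, 0.5), the bias is 0.05-0.10 SD with rejection of 6-10% at 17-20% loss. At 40% loss it is 0.12-0.20 SD with rejection of 9-20%. With d = 0 or p = 0 the bias is zero and rejection is the nominal 5%.

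**The case against.** The strongest reply is that this is silence in a condensed article. The text says when the form is handed out and whom it is for. It does not say that absentees will not be followed up, and a fuller protocol may provide for that. Pairing and the reporting of leavers are matters for an analysis plan. This stands against any claim that absent members cannot be scored, or that the two meetings are the only permitted occasions. A reader might infer that from the wording, but the text does not forbid another route. What remains is narrower: the article does state a collection rule, and that rule, followed as written, misses part of its stated target.

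Other parts of the reply also stand:

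- The document gives no turnover figure. The Discussion does mention "and lack of staff time", but as a barrier to guideline uptake in facilities generally, not as a cause of drop-out from the groups. The section on recruitment funds 0.1 EFT for the falls resource nurse and a further 0.1 EFT for other staff time and engagement, which may limit losses.
- A reader might infer that the RPPE will show a spurious gain. The document does not support this: loss, gap and sign are all assumed, and in the mildest case above a fifth of the rejections are false losses.
- The statement that the result covers only those who stayed holds for a paired analysis, and the article does not commit to one.
- The Discussion expects action research to empower staff but does not mention the RPPE, so the article does not itself rest that expectation on this scale. Meeting transcripts and project diaries also record members' views.
- Giving the closing form to people on the day they leave would mix short and long follow-up. The fix therefore uses one common time point.

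**Conclusion.** The point holds as a cheap improvement. The described procedure ties both RPPE scores to attendance at two meetings about 12 months apart, and nothing else in the article gives leavers or absentees a route to a closing score. The resulting change may not describe the average recruited member.

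The size and direction of any bias cannot be derived from the document. The range of 0.05-0.20 SD is an illustration that rests wholly on the assumed 17-40% loss and 0.3-0.5 SD gap in favour of stayers. The upper end, with about 20% rejection in place of 5%, needs the largest loss and the largest gap together. The RPPE is a secondary process measure. The falls-rate model and the power statement do not use it and are unaffected.

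**What to change.** Amend the RPPE sentence in the Action research section so that every member who completed the first RPPE is offered the closing RPPE at one common time point, when the FARG ends. Those absent from the last meeting or no longer in the group would receive it by mail or e-mail.

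Make the main RPPE comparison the paired change in all members with a first form, whether or not they were still in the group. Report how many have no closing form, and compare their first-meeting scores with those of members who were followed.

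The cost is a sentence or two of text and a few extra forms sent by project officers already in post. Under the assumed losses this is about 45 × 1/6 = 7.5 to 54 × 0.40 = 21.6, so roughly 8-22 forms. The downsides are small: some forms will be completed outside the meeting, and some leavers will not reply, so the missing scores are reduced but not removed.
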